### Recruitment

We recruited upper secondary schools and schools of health and social care through emails to headmasters/headmistresses, online information meetings, and advertisements on our webpage (www.mindfulness.au.dk) and social media between May 2019 and October 2019. We informed the headmasters/headmistresses as well as interested teachers that schools would be randomised to begin teacher training in 2020 or in 2021. Furthermore, it was obligatory for each teacher to include one class with 15 to 30 students. Due to the logistics of teacher planning, it was not possible to include students before the randomisation of schools.

### Randomisation

#### Sequence generation

The schools were allocated into intervention or control schools in two runs: one for each type of school. Each school received a random number, and then the schools were sorted according to the number of teachers included in the project (1 or 2–4) and the random number. The schools on the list were then alternately allocated to intervention or control starting with a control. This procedure was used to try to balance the two arms according to the teachers included in the project. The allocation was performed using Microsoft Excel.

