#### Allocation concealment mechanism

The allocation was performed by the third author, who was not involved in the recruitment, implementation, or data collection. The third author received a list of the schools with an anonymous ID concealing the true identity of the schools and whether or not each school had one or more teachers included in the project. The school were then allocated to control or intervention, as described above. After this, the third author received a list with the true identities of the schools; these were then merged onto the schools before the allocations were sent to the second author.

The characteristics of the schools are shown in Table 2.

**Table 2 Tab2:** Characteristics of included schools in the project

Characteristics	Upper secondary schools		Schools of health and social care	
	Intervention schools, *n* = 15	Control schools, *n* = 15	Intervention schools, *n* = 6	Control schools, *n* = 7
Total number of teachers	21	23	15	17
Number of teachers				
1 teacher	12	9	1	2
2 teachers	1	4	2	1
3 teachers	1	2	2	3
4 teachers	1	0	1	1

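### The stated alternation rule cannot produce Table 2 for upper secondary schools: 12 vs 9 single-teacher schools, where 11 vs 10 is the widest split possible

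*Protocol article*

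**What the plan says.** Under Sequence generation, the protocol article describes the allocation in four statements:

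- Runs: "The schools were allocated into intervention or control schools in two runs: one for each type of school".
- Sort: "the schools were sorted according to the number of teachers included in the project (1 or 2–4) and the random number".
- Rule: "The schools on the list were then alternately allocated to intervention or control starting with a control".
- Purpose: "This procedure was used to try to balance the two arms according to the teachers included in the project".

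Under Allocation concealment mechanism, the person who made the allocation is said to have held, for each anonymised school, only whether it had one teacher or more. That agrees with a two-level teacher group at allocation.

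Table 2 in the same section, captioned "Characteristics of included schools in the project", gives the result by school type and arm. For upper secondary schools it shows 15 schools per arm. Single-teacher schools number 12 in intervention and 9 in control. Schools with two, three and four teachers number 1, 1 and 1 in intervention and 4, 2 and 0 in control.

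The article reports no school changing teacher group, no replaced school and no departure from the rule.

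**The concern.** The rule and the result stand next to each other and cannot both be right as written. A list sorted by teacher group and allocated in strict alternation balances that group almost perfectly by construction. A difference of three schools in each group is outside what the procedure can deliver.

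The matter goes beyond tidiness for two reasons. First, under Recruitment each teacher had to bring one class, so teacher counts fix the number of classes and how they cluster within schools. In upper secondary schools, Table 2 puts 9 of 21 intervention classes (43%) and 14 of 23 control classes (61%) in multi-teacher schools. Second, students could be included only after schools were randomised, teachers registered the classes themselves, and neither providers nor participants were blinded. A reader therefore needs to know whether Table 2 shows the counts used for allocation or counts from a later date, and whether the described procedure is the one that was run.

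**Working it through.** **Inputs** (Table 2, Sequence generation, Trial status)

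| | Upper sec., intervention | Upper sec., control | Health/social, intervention | Health/social, control |
|---|---|---|---|---|
| 1 teacher | 12 | 9 | 1 | 2 |
| 2 teachers | 1 | 4 | 2 | 1 |
| 3 teachers | 1 | 2 | 2 | 3 |
| 4 teachers | 1 | 0 | 1 | 1 |

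**Step 1: is the table sound in itself?** Schools: 12+1+1+1 = 15; 9+4+2+0 = 15; 1+2+2+1 = 6; 2+1+3+1 = 7. Teachers: 12+2+3+4 = 21; 9+8+6+0 = 23; 1+4+6+4 = 15; 2+2+9+4 = 17; total 76. These match the printed totals and the 44 + 32 teachers under Trial status. The mismatch is therefore not caused by a broken table.

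**Step 2: what the rule allows.** After the sort, each teacher group is one unbroken block of m schools. Strict alternation splits a block into m/2 rounded up and m/2 rounded down, so the arms differ by at most one.

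*Health and social care*, 3 single and 10 multi, starting with control: single 1 intervention, 2 control; multi 5 and 5; total 6 and 7. Table 2 is reproduced exactly, whichever group comes first.

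*Upper secondary*, 21 single and 9 multi, starting with control:

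| | Single, I vs C | Multi, I vs C | Total |
|---|---|---|---|
| Single-teacher schools first | 10 vs 11 | 5 vs 4 | 15 vs 15 |
| Multi-teacher schools first | 11 vs 10 | 4 vs 5 | 15 vs 15 |
| Table 2 | 12 vs 9 | 3 vs 6 | 15 vs 15 |

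Starting with intervention, restarting the alternation at the group boundary, or sorting on the exact count (1, 2, 3, 4, in any order) also gives only 10 vs 11 or 11 vs 10 single-teacher schools.

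**Step 3: how much must have changed, if schools only changed teacher group?** Keep the 30 schools in their arms and let the number of single-teacher schools at allocation vary. Each change of group moves the intervention-minus-control difference in single-teacher schools by one. Table 2 has +3.

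- Multi-teacher schools first: the rule can give at most +1, so at least two schools changed. Three starting points need exactly two:
  - 23 + 7 gives 12 vs 11 single; two control schools gain teachers.
  - 19 + 11 gives 10 vs 9 single; two intervention schools fall to one teacher.
  - 21 + 9 gives 11 vs 10 single; one school changes in each arm.
- Single-teacher schools first: the rule can give at most 0, so at least three changed. From 24 + 6 (12 vs 12), three control schools suffice; from 18 + 12 (9 vs 9), three intervention schools suffice.

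**Step 4: what if the random number led the sort?** The teacher group would then have no effect on the order, and the number k of single-teacher schools in intervention would follow P(k) = C(21,k)·C(9,15−k)/C(30,15). This gives P(12) = 0.16 and P(difference of three or more, either direction) = 0.43. A 12 vs 9 split would be unremarkable, but the sort would not have served its stated purpose.

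**The case against.** The strongest reply is that this is a reporting question about a finished allocation. Table 2 carries no date and does not say that it shows the counts used for allocation. Its 76 teachers equal the number given as having consented under Trial status, which lends no support to a story of losses after allocation. The wording of the sort could be loose. Upper secondary teacher totals are 21 vs 23, a gap of two, and the health and social care schools, which fit the rule, show the same gap (15 vs 17). All of this stands. It limits what can be concluded, but it does not remove the contradiction.

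Three stronger readings are tempting, and the article does not support them:

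- A reader might infer that intervention schools lost teachers while control schools gained them. Step 3 shows that changes in one arm alone are enough.
- A reader might infer that either teacher numbers changed or the rule was broken. A table error, replaced schools or a misdescribed sort order fit equally well.
- A reader might fear adjustment for a variable determined after allocation. The model under Statistical methods contains no teacher-count term, so the plan as written does not do this.

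**Conclusion.** The description of the allocation and Table 2 disagree for upper secondary schools. The difference is three schools in each teacher group against a maximum of one. This assumes that teacher group was the leading sort key, as the text and its stated purpose imply, and that Table 2's 21 and 9 are the counts at allocation. If those counts changed later, at least two schools changed group, possibly all in one arm.

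The explanations are teacher numbers that changed after allocation, replaced schools, a table error, a sort led by the random number, or a departure from the rule. The article cannot separate them. The mismatch does not by itself show subversion or bias, and intention-to-treat analysis is already planned. What is established is that the stated procedure or the stated result needs correcting.

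**What to change.** 1. Check the existing Excel allocation file for the sort order, each upper secondary school's teacher group at allocation, and the arm assigned.
2. Correct whichever of Sequence generation or Table 2 is wrong. If any school was replaced or not placed by the rule, say so.
3. Report Table 2 by the teacher group used at allocation, and list later changes in teacher numbers by arm with reasons. Reasons for teachers opting out were already being registered.
4. If the sort by teacher group was used, add the as-allocated teacher group and school type as fixed effects to the repeated measurement model. Both shaped the allocation, and neither is among the systematic effects listed. Use the allocation-time group, not a later count.

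The cost is a check of an existing file, a corrected table or paragraph, and two covariates. No new data are needed.

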#### Allocation concealment mechanism

The allocation was performed by the third author, who was not involved in the recruitment, implementation, or data collection. The third author received a list of the schools with an anonymous ID concealing the true identity of the schools and whether or not each school had one or more teachers included in the project. The school were then allocated to control or intervention, as described above. After this, the third author received a list with the true identities of the schools; these were then merged onto the schools before the allocations were sent to the second author.

The characteristics of the schools are shown in Table 2.

**Table 2 Tab2:** Characteristics of included schools in the project

Characteristics	Upper secondary schools		Schools of health and social care	
	Intervention schools, *n* = 15	Control schools, *n* = 15	Intervention schools, *n* = 6	Control schools, *n* = 7
Total number of teachers	21	23	15	17
Number of teachers				
1 teacher	12	9	1	2
2 teachers	1	4	2	1
3 teachers	1	2	2	3
4 teachers	1	0	1	1

### Blinding

Neither intervention providers nor study participants were blinded.

### Data collection and management

Quantitative data were collected and stored using the Research Electronic Data Capture (REDCap) tool hosted by Aarhus University [46]. The included teachers were asked to register the class recruited for the research project, to provide students (including absentees) with online access to the three questionnaires (baseline, 3- and 6-month follow-up), and to arrange a time for students to complete the questionnaires during school hours. Teachers and students received two reminders in case of non-respondence.

We informed the students about the trial and the option to opt out and not completing the questionnaires. Data collection procedures have been pilot-tested and improved several times. Reasons for teachers to opt out of the trial were registered continuously. Furthermore, we registered participation in the teacher training programme and also the teaching of the mindfulness programme. The teachers were asked to report adverse events through their teaching period. Teachers have access to supervision from psychologists and psychiatrists to ensure prevent harm and to take good care of participants who may suffer harm from trial participation.

After implementing the “On Top of Everything” programme, teachers in the intervention group were invited to participate in focus group interviews. The teachers were asked about their experience of implementing mindfulness in their schools and about which facilitators and barriers they encountered through the process.

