## Aims

Our primary aim is to evaluate the effectiveness of a teacher training programme to teach the mindfulness programme “On Top of Everything” as part of regular classroom teaching in Danish upper secondary schools and schools of health and social care on students’ self-reported mental well-being 6 months from baseline. Secondary aims are (1) to evaluate the effectiveness in a vulnerable subgroup as well as in the total population of students 3 and 6 months from baseline using other outcome measures on mental health and (2) to investigate the facilitators and barriers among teachers to implement mindfulness in schools.

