### Statistical methods

Quantitative data will be analysed according to the intention-to-treat principle using a repeated measurement model with the systematic effect: gender, age, class, time (three time points), intervention, interaction between time and intervention, and random effect of school, teacher/class within school, and student within class. Confidence intervals and standard errors will be found by bootstrapping to adjust for possible deviation from the normality of the random effects. Exploring subgroup analysis will be conducted on gender, a vulnerable subgroup (the 15% with the lowest SWEMWBS score), and type of school. To take account of missing data, we will perform four sensitivity analyses representing scenarios with data not missing at random. Missing outcomes will be substituted with the model-based prediction adding or subtracting 0.02 SD in the intervention or control arm.

Qualitative data will be transcribed and analysed based on qualitative content analysis. Each focus group interview will be read and notes will be taken, and themes will be introduced, organised, and related to quotes that are open to interpretation and that continue to an analytic investigation and connection of themes and quotes from all focus group interviews.

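### If an intervention teacher's opt-out removes both the teaching and the follow-up scores, the planned model credits those students with the taught effect, and the four 0.02 SD sensitivity analyses cannot show it

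*Protocol article*

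**What the plan says.** The Aims section describes the object of evaluation as "a teacher training programme to teach the mindfulness programme “On Top of Everything” as part of regular classroom teaching", so the class teacher is the route by which students receive the programme.

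Data collection and management gives the same teachers the measurement task. They were asked "to provide students (including absentees) with online access to the three questionnaires", and also "to arrange a time for students to complete the questionnaires during school hours". There was a second contact route: "Teachers and students received two reminders in case of non-respondence". On withdrawal the section says "Reasons for teachers to opt out of the trial were registered continuously". It adds that attendance at the teacher training and the teaching of the programme were recorded. It does not say whether a class was still followed after its teacher left.

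Statistical methods states: "Quantitative data will be analysed according to the intention-to-treat principle using a repeated measurement model". The model has time, intervention and their interaction, with random effects for school, teacher/class and student. For data not missing at random there are four sensitivity analyses: "Missing outcomes will be substituted with the model-based prediction", shifted up or down by 0.02 SD in one arm or the other.

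**The concern.** The aim is the effectiveness of training teachers to teach mindfulness. A randomised intervention teacher who never teaches is part of that effectiveness, and an intention-to-treat estimate should be diluted accordingly.

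The dilution is lost if the event that stops the teaching also stops the measurement. Students with only a baseline score then contribute nothing to the estimated change, and the model implicitly assigns them the mean change of the observed intervention classes. Their baseline cannot correct this, because it precedes teaching and carries no information on whether the class was taught. A random class effect that is constant over time cannot correct it either. Whether the class was taught is not in the model.

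The mechanism is one-sided: a control teacher's withdrawal loses data but no programme. If the programme helps, the estimate moves away from the null, towards the effect in classes where teaching took place.

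**Working it through.** **Inputs from the protocol article**
- Target difference 1 SWEMWBS point; within-person SD 2.4; SD of change 3.5; 80% power; 194 per group (Sample size).
- Intervention teachers 21 + 15 = 36; control teachers 23 + 17 = 40 (Table 2). One class per teacher (Recruitment).
- Sensitivity shift 0.02 SD (Statistical methods). The article does not say which SD, so both 2.4 and 3.5 are used.

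**Assumptions, because the article gives no figure**
- Share p of intervention students untaught and unobserved after baseline: 10%, 20%, 30%.
- Effect 1 point in taught classes and 0 in untaught classes.
- For the model check: 15 students per class (the lower end of the stated 15 to 30), SD 3 between students and 0.5 between classes.
- Two-sided alpha of 0.05 for the sample-size check.

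**Step 1: the plan's own figure.** n = 2 × (1.960 + 0.842)² × 3.5² / 1² = 192.3, so 193 per group. The t-test version gives 193.26, so 194. The stated figure reproduces; the 1-point target and the SD of 3.5 are used below as the plan uses them.

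**Step 2: true intention-to-treat effect.** (1 − p) × 1 + p × 0 gives 0.9, 0.8 and 0.7.

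**Step 3: what the model targets.** The expected value of the generalised-least-squares estimate of the time-by-intervention term at 6 months was computed for 36 intervention and 40 control classes, with student and class random effects. The school effect and the covariates were left out.

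| Intervention classes out | Follow-up lost | Follow-up still collected | True ITT effect |
|---|---|---|---|
| 4 of 36 | 1.00 | 0.89 | 32/36 = 0.89 |
| 7 of 36 | 1.00 | 0.81 | 29/36 = 0.81 |
| 11 of 36 | 1.00 | 0.69 | 25/36 = 0.69 |

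If follow-up is lost, the overstatement is p × 1 point, a ratio of 36/32 = 1.13, 36/29 = 1.24 or 36/25 = 1.44. If follow-up continues, it is zero.

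**Step 4: what the planned sensitivity analyses can show.**
- Shift per missing score: 0.02 × 2.4 = 0.048 to 0.02 × 3.5 = 0.07 points.
- Effect on the estimate: p × shift, from 0.10 × 0.048 = 0.005 to 0.30 × 0.07 = 0.021 points.
- Shift needed to remove the credited effect: 1 point, which is 1/0.07 = 14 to 1/0.048 = 21 times the planned shift.
- Example at p = 20% and SD 3.5: shifting the intervention arm down gives 1.00 − 0.20 × 0.07 = 0.986, against a true 0.80.

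**The case against.** A reader might infer that a teacher's opt-out ends questionnaire access, and hence that the planned analysis does overstate the programme. The article does not support this. It never says that access stops, the questionnaires were online, and students as well as teachers received reminders.

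The mechanism is also narrow. Training ran for about a year, and teaching took place in spring 2021. A teacher who left before baseline contributes no student scores, so nothing can be imputed from a baseline. A teacher who left after the 10 sessions loses data from students who were taught. Only loss after baseline and before teaching gives the full effect shown above.

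The size is assumed throughout: the article gives no opt-out count, and the p × 1 result follows directly from the inputs. With no effect in taught classes there is no bias. All of this stands, and it makes the point conditional.

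It can also be argued that the handling of teacher withdrawal belongs in an analysis plan that is not shown. That stands only in part. The article does not leave missing data open: it fixes the number of scenarios, their centre and their shift. None of the four, as described, uses the opt-out and teaching records that the trial holds.

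Making a control-based imputation the primary estimate would go too far. It replaces one untestable assumption with another, and it is pulled towards the null if partial teaching helps.

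**Conclusion.** The point holds conditionally. Delivery and measurement run through the same teacher, so loss of both together is plausible. Where it occurs, the planned model targets the effect in classes that were taught and observed. On a 1-point effect the overstatement is 0.1, 0.2 or 0.3 points for 10%, 20% or 30% of intervention students affected.

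This requires four things together: baseline collected, teaching not delivered, follow-up lost, and a real effect in taught classes. It also assumes that untaught students change as control students do. The documents do not show how often this pattern occurred, so they do not establish that the trial's estimate is biased.

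One part does not depend on the opt-out count: shifts of 0.048 to 0.07 points around the same prediction cannot reveal the problem if it exists.

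**What to change.** In Statistical methods, keep the planned primary model and add one named sensitivity analysis. Use the registered opt-out and teaching records to identify intervention students whose class was not taught. Multiply impute their missing 3- and 6-month SWEMWBS from the control-arm trajectory given their own baseline, and leave them in their randomised arm. Treat partly taught classes as a separate scenario.

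Report teacher opt-outs by arm and by timing (before baseline, between baseline and teaching, during teaching, after teaching), and state whether those classes were still sent questionnaires. The last follow-up was collected in autumn 2021, so this can only be a report of what was done.

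Cost: one extra imputation run and a few lines of reporting, on records already held and with analysis planned from the beginning of 2023. The sensitivity estimate may be less favourable than the primary one, and it is conservative if partial teaching helps. If such classes were few, the two will nearly agree.

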### Statistical methods

Quantitative data will be analysed according to the intention-to-treat principle using a repeated measurement model with the systematic effect: gender, age, class, time (three time points), intervention, interaction between time and intervention, and random effect of school, teacher/class within school, and student within class. Confidence intervals and standard errors will be found by bootstrapping to adjust for possible deviation from the normality of the random effects. Exploring subgroup analysis will be conducted on gender, a vulnerable subgroup (the 15% with the lowest SWEMWBS score), and type of school. To take account of missing data, we will perform four sensitivity analyses representing scenarios with data not missing at random. Missing outcomes will be substituted with the model-based prediction adding or subtracting 0.02 SD in the intervention or control arm.

Qualitative data will be transcribed and analysed based on qualitative content analysis. Each focus group interview will be read and notes will be taken, and themes will be introduced, organised, and related to quotes that are open to interpretation and that continue to an analytic investigation and connection of themes and quotes from all focus group interviews.

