### Sample size

We assume a 1-point increase between-group effect in SWEMWBS to be of public health relevance [44, 45]. From another study that analysed the intervention effect on SWEMWBS in a mixed model with three repeated measurements, and where cluster levels of teacher and school were taken into account, we found a within-person SD = 2.4. To detect an effect on 1 score point in SWEMWBS change, SD = 3.5 = SQRT (2) × 2.4 with 80% power, will require 194 participants in each group, 388 participants in total.

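### The 0.02 SD shifts in the missing-data sensitivity analyses are too small to represent outcomes not missing at random; a relaxed within-student covariance is a cheap second safeguard

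*Protocol article*

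**What the plan says.** All of this is in the protocol article, Statistical methods, unless noted.

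- **Missing data:** "we will perform four sensitivity analyses representing scenarios with data not missing at random". The rule is "Missing outcomes will be substituted with the model-based prediction adding or subtracting 0.02 SD in the intervention or control arm". The article does not say which SD is meant.
- **Model:** the fixed part includes "time (three time points), intervention, interaction between time and intervention", and the random part is "random effect of school, teacher/class within school, and student within class". No random slope and no residual covariance is stated.
- **Inference:** "Confidence intervals and standard errors will be found by bootstrapping to adjust for possible deviation from the normality of the random effects".
- **Subgroups:** "Exploring subgroup analysis will be conducted on gender", for type of school, and for "a vulnerable subgroup (the 15% with the lowest SWEMWBS score"). The time at which the lowest 15% is defined is not given. Aims lists the vulnerable subgroup under the secondary aims.
- **Target (Sample size):** "We assume a 1-point increase between-group effect in SWEMWBS to be of public health relevance". The within-person SD is 2.4 and the SD of change 3.5.
- **Context:** Blinding states that neither providers nor participants were blinded. No dropout rate is given anywhere.

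**The concern.** A sensitivity analysis for outcomes not missing at random should show how far the missing students would have to differ from the model's prediction before the conclusion changes. That requires shifts of a size that could plausibly occur. The article fixes one size, and it is very small against both the target effect and the precision of the trial. If the rule is followed as written, the report will call the primary result robust almost whatever the missing students' true scores were.

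This matters because the arms are unblinded, teachers arrange the completion of questionnaires, and only intervention classes receive the programme during follow-up. Non-response related to well-being and differing by arm is therefore possible, although no figure in the article shows that it occurred.

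The second, conditional matter is the covariance. A likelihood model handles dropout that depends on observed earlier scores only if its within-student covariance is right. A student intercept with independent, equal-variance residuals gives the same variance at all three times and the same correlation between each pair. The bootstrap does not change the point estimate, so it cannot repair a bias arising here.

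**Working it through.** **1. The plan's own figure.** Inputs from Sample size: difference 1, SD 3.5, power 80%; two-sided alpha 0.05 is assumed. n per group = 2 × (1.960 + 0.842)² × 3.5² / 1² = 192.3, so 193; the t-test version gives 193.3, so 194. The stated 194 per group reproduces with the rounded SD (√2 × 2.4 = 3.39 would give 181). The SD of 3.5 is therefore the plan's working value, and I use it below.

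**2. Size of the shift.** Movement of an arm mean = 0.02 × SD × fraction missing. The fraction missing is assumed.

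| SD | Missing | One arm | Arms opposed |
|---|---|---|---|
| 2.4 | 10% | 0.005 | 0.010 |
| 3.5 | 10% | 0.007 | 0.014 |
| 3.5 | 30% | 0.021 | 0.042 |
| 3.5 | 40% | 0.028 | 0.056 |
| 5 | 40% | 0.040 | 0.080 |

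The upper bound at SD 3.5 needs no dropout assumption: if every 6-month score in an arm were missing, that arm would move 0.02 × 3.5 = 0.07 points, 7% of the 1-point target.

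**3. Against precision.** With the plan's 194 per group and SD 3.5, SE = √(2 × 3.5² / 194) = 0.355. At 30% missing the opposed shift is 0.042 / 0.355 = 0.12 SE. Only a result with z between 1.96 and 2.08 (p between about 0.038 and 0.05) could lose significance. The one-arm shift is 0.06 SE.

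**4. Shift needed to change a conclusion.** For illustration, assume an observed effect of 0.7 with SE 0.3 (p about 0.02) and 30% missing in the intervention arm. Tipping shift = (0.7 − 1.96 × 0.3) / 0.30 / 3.5 = 0.107 SD, over five times the shift planned.

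**5. Covariance, total population (conditional).** This is a large-sample simulation with true effect 0, total SD 4 at baseline, and school and class effects left out. The 6-month dropout depends on the 3-month score. The model has a student random intercept with independent, equal-variance residuals. SD 4 and within-person SD 2.4 imply a correlation of 1 − 2.4²/4² = 0.64. Bias in the 6-month contrast, over four covariance patterns with correlations that decay, SDs that rise, or both:

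| Dropout | Total population | Lowest 15% at baseline, separate fit |
|---|---|---|
| Equally selective in both arms | about 0 | about 0 |
| Low scorers leave, 30% against 15% | 0.02 to 0.07 | 0.06 to 0.17 |
| Selective in one arm only, 25% each | 0.03 to 0.11 | 0.11 to 0.30 |
| Opposite selection, 25% each | 0.05 to 0.25 | 0.22 to 0.64 |
| Opposite selection, 40% each | 0.08 to 0.35 | 0.36 to 0.99 |

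The subgroup column also includes a population in which equal variance and correlation hold exactly. In that case the total-population bias is 0. If dropout instead follows the 0-to-3-month change in one arm only, with 30% missing, the total-population bias is 0.06 to 0.10 with correlations 0.67/0.67/0.58, and 0.15 to 0.22 with 0.70/0.70/0.52. An unstructured covariance, or its regression equivalent, stayed within about 0.03 of zero throughout, which is simulation noise.

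**6. Why the subgroup differs.** Take a normal score with every correlation 0.64 and select the lowest 15% at baseline (cut-off −1.036, mean −1.554).

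- Baseline variance: 1 + 1.036 × 1.554 − 1.554² = 0.19 of the population's.
- Follow-up variance: 1 − 0.64² × (1 − 0.195) = 0.67.
- Baseline to follow-up correlation: 0.64 × √(0.195 / 0.67) = 0.35.
- 3-to-6-month correlation: (0.64 − 0.64² × 0.805) / 0.67 = 0.46.

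Equal variance and equal correlation therefore fail within the subgroup even when they hold in the population.

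**The case against.** **On the shift.** The SD is not named, so the points per missing value are not fixed by the article, and any wider range is a matter of judgement. Both statements are true, but neither rescues 0.02: with SD 5 and 40% missing, the opposed shift is still only 0.08 points.

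**On the covariance.** A reader might infer that the listed random effects force equal variance and correlation, so that selective dropout biases the 6-month effect. The article does not support that. It states no residual covariance; a structured residual can sit beside a student intercept, and such detail may be in an analysis plan that is not shown. Bias also needs two things together: a wrong covariance, and dropout whose rate or selection differs by arm. No figure in the article shows either. Completion in school hours, access for absentees and two reminders work against heavy loss. The total-population bias is small in most scenarios, and the largest values need opposite selection in the arms. The subgroup result assumes selection at baseline and a separate fit, in an analysis labelled exploratory. With about 0.15 × 1100 = 165 students, an unclustered SE is about √(2 × 3.5² / 82.5) = 0.54, larger than most of the biases shown. These objections stand, and they make the covariance a secondary and conditional point.

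**On linking the two.** It is tempting to say that the 0.02 SD shifts are too small to reveal the covariance problem. That does not follow. Shifts are added to the same model's predictions and carry over its covariance error, so they are not a test of that error at any size. The two matters are separate.

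**Conclusion.** The shift size is a real defect in a rule that the article states outright. At SD 3.5 it moves the 6-month contrast by 0.021 to 0.042 points with an assumed 30% missing, and by no more than 0.07 per arm at any missing rate. The four analyses do not represent the departures from missing at random that they are said to represent, and they can change only a conclusion already at the boundary. The conclusion rests on 3.5 being the SD meant; over SDs of 2.4 to 5 and 10 to 40% missing it does not alter.

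The covariance matter holds only conditionally. If residuals are independent with equal variance, dropout that depends on earlier scores and differs between arms can bias the contrast. The bias is usually about 0.1 points or less in the total population, and larger in a separately fitted lowest-15% group defined at baseline. Total SD, dropout rates, dropout rules and correlation patterns are all assumptions.

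**What to change.** 1. **Shifts (main change).** Name the SD, and replace the single 0.02 by a range large enough to matter, for example 0.1 to 0.5 SD of the SWEMWBS score, in each arm separately and in opposite directions. At SD 3.5 and 30% missing, that range moves the contrast by 0.105 to 0.525 points in one arm, or 0.21 to 1.05 opposed. Report the shift at which the primary conclusion changes, so that readers can judge whether it is plausible. The end points are a choice; the tipping shift is the result that matters.
2. **Covariance (secondary).** State an unstructured 3x3 within-student covariance in place of the student intercept, and keep the school and class terms. Estimate it afresh in any model fitted within the lowest 15%, and name in advance a simpler structure in case it cannot be estimated there: about 165 students over 76 teachers is roughly two per class.

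The cost is two sentences, a little extra analysis and about four more covariance parameters with about 1100 students. No new data are needed, and Trial status says that analysis was still to begin. The downside is that the sensitivity results may look less robust.
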